**Figure 1 f1:**
[figure not shown]
Study timeline.

#### Participants

Participants in the *Nurturing Moms* study will be recruited through various channels: clinical/health settings, community outreach recruitment events and community organizations, Research Match, and UMiamiHealthResearch.org. Participants will undergo a screening process in which they must meet the following inclusion criteria: 18 years old or older, speaks and understands English, Black or Latina. Additionally, they must be pregnant (less than 36 weeks) or postpartum (up to 12 months after birth). Participants will be disqualified from inclusion in the study based on the following exclusion criteria: a diagnosis of psychosis, inability to speak or understand English, or being neither pregnant (>36 weeks) nor postpartum (up to 12 months). Individuals with a history of seizures, vertigo, significant vision or hearing impairment, significant motion sickness, epilepsy, or sensitivity to flashing light/motion are also excluded from participation. Injuries to the eyes, face, neck, or arms that would make the use of the hardware uncomfortable are also grounds for exclusion. The implementation of these criteria enhances internal validity, optimizing the relevance and reliability of research findings. We aim to enroll 50 participants (25 expectant and 25 postpartum).

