**Methods:**

The Nurturing Moms study uses a pre- and post-intervention design with a 5-week NurtureVR program. Fifty participants, 25 expectant and 25 postpartum Black and Latina women, will be recruited through clinics, community organizations, and online platforms. The study involves three phases: baseline assessments of stress, mood, self-efficacy, demographics, and health history; daily use of NurtureVR for 15 minutes during the third trimester and six weeks postpartum; and follow-up assessments at six weeks postpartum. The program includes 49 modules on labor and delivery, stress during pregnancy, nutrition, breastfeeding, hormonal changes, 3D VR representations of fetal development, pain management simulations, and mindfulness exercises for labor. Participants will report stress, anxiety, mood, and pain levels following each VR session. Additional qualitative insights will be gathered through focus groups, and an optional survey will be administered one-year post-intervention to evaluate long-term effects.

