### Study procedures

#### Timeline

The Nurturing Moms study will assess the effectiveness of NurtureVR, a digital solution for maternal mental health, across four phases. In phase I, participants will be recruited from health clinics, community-based organizations, and online platforms. Interested individuals will receive a screening form link via REDCap to determine eligibility based on inclusion and exclusion criteria (described below). Eligible participants will be contacted by a study team member to review and electronically sign an informed consent form before completing a 10–20-minute baseline questionnaire on the same platform.

In Phase II, VR headsets will be shipped to participants one week after the baseline questionnaire is completed. Participants will use the NurtureVR for five weeks and will be asked to rate their level of stress, anxiety, mood, and pain level after each VR session using well-validated scales. In Phase III, participants will repeat the surveys three months after completion of the digital intervention. Additionally, two focus group sessions will be held with five participants each, focusing on Black and Latina expectant and postpartum women’s views on resilience, their NurtureVR experiences, perceptions, and recommendations for using VR for stress management. Each focus group will be conducted online to ensure accessibility, with one session scheduled before and one after the participants’ completion of the NurtureVR program. Discussions will follow a semi-structured format, encouraging open dialogue around key themes such as resilience and VR experience. For data analysis, we will employ thematic analysis, using NVivo software to organize and code responses. This approach allows for consistent identification of recurring themes, patterns, and variations in participants’ feedback, facilitating a thorough understanding of their experiences and recommendations. Coding will be iterative and conducted by multiple researchers to enhance reliability and capture diverse perspectives.

The final phase, which is optional, invites participants to repeat the surveys one year after completing NurtureVR. This comprehensive approach aims to provide a thorough evaluation of NurtureVR’s impact on maternal mental health in the short and longer term (See **Figure 1**).

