#### Study settings

This is a 5-week home-based study primarily using a virtual reality headset to engage in NurtureVR. Participants can set up, customize, and navigate the program through the RealizedCare mobile or web application, which serves as the platform for their participation and is free of cost to the participants. This application is compatible with any cellular device, tablet, or desktop. Mi-Fi devices will be provided to participants who do not have reliable access to Wi-Fi. Participants will be actively encouraged to use the VR headset regularly, by completing at least one module each week (see **Table 1** for module content).

**Table 1 T1:** NurtureVR module content.

Education Topic		Mindfulness Topic
Pre-natal (Before birth)		
Week 1	Power of VR on Mental Health During Pregnancy	Progressive Relaxation sequence
Week 1	Impacts of Acute and Chronic Stress During Pregnancy Techniques to Cope	Turning off Your Stress Response
Week 2	Introduction to Mindfulness and Meditation	Mindfulness: Awareness of Breath
Week 2	Staying Active During Pregnancy	Mindfulness of Body
Week 2	Sleep and Stress During Pregnancy	Relaxing & Letting Go of Thoughts
Week 3	What is a C-Section and Why Would I need it?	Being Present I (Deattachment to Outcomes*)
Week 3	Baby’s Almost Here: Enjoying the Final Weeks of Pregnancy	Mindfulness of the Life Growing Within
Week 3	Baby’s Almost Here: Advantages of Going Full Term	Being Presence II (Deattachment of Outcomes)
Week 4	Stages of Labor	The Healing Power of Breath
Week 4	Pain Management During Labor	Letting Go of Resistance to Sensations
Week 4	Should Hypnotherapy Be in the Delivery Room?	Deepening Awareness
Week 4	What is Lamaze?	Breathing Through the Whole Body
Week 5	Handling Stress and Breastfeeding	Cultivating Connection with Your Baby I
Week 5	Breastfeeding Newborn	Cultivating Connection with Your Baby II
	Lactation Support 2	Honoring Your Body As it Is
All Weeks	Baby This Week module	
Labor (Optional)	How to Use VR During Labor to Reduce Pain	
Postpartum (anyone 6 months after giving birth)		
Week 1	10 Reasons Skin to Skin is Good for Your Baby and You	Cultivating Connection with Your Baby (Redux)
Week 1	Down-There Care: Recovery from Delivery Part 1	Healing is a Powerful Piece of the Journey
Week 2	Postpartum Nutrition	Intuitive Eating/Honoring Your Body’s Needs
Week 2	Sexual Health After Pregnancy	Mindfulness as Empowerment/Acknowledging & Making Choices About Desires

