
#### NurtureVR

The NutureVR mobile app will be installed on the participants’ mobile device. With 49 modules, the program will span five weeks prenatal, optional use during labor, and five weeks postpartum (available for anyone up to six months after childbirth). These modules are aimed to serve as a sanctuary for learning and stress relief, offering education and support for the entire family while fostering intimate connections and bonding to benefit the well-being of the mother and baby. Key features of NurtureVR include education on the effects of stress during pregnancy, 3D VR representations of fetal development, pain management simulations, mindfulness exercises for labor, and postpartum guidance covering topics such as hormonal changes, nutrition, emotional regulation, breastfeeding, and lactation training through VR-enabled practice sessions.

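### Women are eligible up to 12 months after birth, but the postpartum programme is stated to be available only to six months; late prenatal enrollees may also run out of time

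*Protocol article*

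**What the plan says.** All references are to the protocol article.

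- **Participants, inclusion:** "they must be pregnant (less than 36 weeks) or postpartum (up to 12 months after birth". The exclusion criteria repeat the 12-month limit: "being neither pregnant (>36 weeks) nor postpartum (up to 12 months". The target is 25 expectant and 25 postpartum women. No lower limit of gestation is given.
- **NurtureVR:** "the program will span five weeks prenatal, optional use during labor, and five weeks postpartum (available for anyone up to six months after childbirth".
- **Study settings, Table 1:** the postpartum block is headed "Postpartum (anyone 6 months after giving birth". This is the same six-month figure, loosely worded. The block of prenatal modules, weeks 1 to 5, is headed "Pre-natal (Before birth".
- **Timeline:** "VR headsets will be shipped to participants one week after the baseline questionnaire is completed". Use then lasts five weeks.
- **Abstract, Methods:** "daily use of NurtureVR for 15 minutes during the third trimester and six weeks postpartum".

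**The concern.** The article gives one time limit for who may enter and a different one for when the postpartum intervention is available. A woman eight months after birth meets every timing criterion, yet lies outside the period in which her programme is said to be on offer. Nothing in the article says what she receives.

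The prenatal side has a milder version of the problem. Entry is allowed until just under 36 weeks, but a week passes before the headset is shipped and the prenatal content takes five weeks.

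The analysis treats everyone as having had a five-week exposure. Adherence is tracked through module start times and completion statuses, and the results are meant to supply effect sizes for larger studies. If some women had only part of the programme open to them, the pre-post change would mix different exposures. A shortfall in use could then reflect the calendar and not the acceptability of NurtureVR.

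**Working it through.** The article gives no figure of its own on this point; its one sample-size calculation plays no part here.

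**Postpartum window**

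Inputs: eligibility 0 to 12 months and 25 postpartum women (Participants); availability to six months (NurtureVR, Table 1).

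- Part of the eligible window beyond the stated availability: (12 − 6) / 12 = 50%.
- Expected number past six months at entry = 25 × share of postpartum entrants past six months.
- The share is not given. With entry uniform over 0 to 12 months (assumption): 25 × 0.50 = 12.5, so 12 to 13 women.
- Range over other shares: 25 × 0 = 0; 25 × 0.25 = 6.25; 25 × 0.75 = 18.75; 25 × 1 = 25. The documents do not narrow this.

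**Prenatal window**

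Inputs: latest eligible gestation 35w6d (Participants); one week to shipment and five weeks of use (Timeline); transit time not stated, taken as zero. Gestation at birth is not given. I assume 37, 40, 41 or 42 weeks to show the range.

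- Latest entrant: 35w6d + 1 week = 36w6d at shipment; 36w6d + 5 weeks = 41w6d at the end of week 5.
- Latest baseline that fits = gestation at birth − 1 week − 5 weeks.
- Weeks left for the latest entrant = gestation at birth − 36w6d, against five needed.

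| Birth at (assumed) | Latest baseline that fits | Weeks left for entry at 35w6d |
|---|---|---|
| 37w0d | 31w0d | 0.1 |
| 40w0d | 34w0d | 3.1 |
| 41w0d | 35w0d | 4.1 |
| 42w0d | 36w0d | 5.1 |

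For a birth at 40 weeks, only baseline after 34w0d is affected, a strip of about two weeks. If entry were uniform over 0 to 36 weeks (assumption), that is 2/36 × 25 = 1.4 women. If it were uniform over 28 to 36 weeks (assumption), it is 2/8 × 25 = 6.25. For a birth at 42 weeks, every eligible woman fits, though only just and with no transit time.

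**Abstract against the other sections**

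The abstract places use in the third trimester and in six weeks postpartum. The eligibility criteria have no lower gestational limit and run to 12 months after birth; the programme description gives six months. The abstract agrees with none of these.

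**The case against.** The strongest reply is that the six-month wording may describe the intended audience, or a limit on starting, and not a technical lock. No section says that the application closes content at six months, and participants set up and navigate the program themselves. This stands. A reader might infer that women past six months cannot receive the intervention; the documents do not show that, only that access is unstated.

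A reader might also carry the arithmetic further: 26 − 1 − 5 = 20 weeks, and (52 − 20)/52 = 61.5%, so about 15 of 25 could not finish inside six months. That needs both uniform entry and content that closes mid-course on the six-month date. Nothing supports the second condition, so the figure should not be used.

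On the prenatal side, the length of pregnancy is my assumption, the problem is confined to late enrollees, and the minimum use asked for is only one module a week. A woman who gives birth mid-course might move on to the postpartum modules. The article gives no rule for this, but the full protocol may. This too stands, and makes the prenatal point secondary.

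Finally, the statistical section names no completion-rate endpoint; it assesses feasibility through the user-experience questionnaires. So the effect on feasibility conclusions is a risk through the adherence data, not a demonstrated bias.

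None of this removes the 12- against six-month conflict. It is not a detail that the article has left to a longer document: both limits are stated, and they disagree.

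**Conclusion.** The point holds in a limited form. The postpartum contradiction needs no outside figure: half of the eligible window lies beyond the stated availability of the programme, and no section resolves it. The estimate of 12 to 13 of 25 women rests on uniform entry and could be anywhere from 0 to 25. Any loss of exposure, and so any dilution of the pre-post change, depends on whether these women can still use the content.

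The prenatal mismatch is lesser and conditional. It depends on the assumed gestation at birth and disappears at 42 weeks with no transit time. The abstract's timing is a further inconsistency to clear up. The conflict should be settled before enrolment, because it decides who enters and what they are offered.

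**What to change.** 1. Reconcile the Abstract (Methods), Participants, Study settings (Table 1) and NurtureVR sections to one postpartum window and one gestational window. Which windows to keep is for the sponsor; this review takes no position.
2. Have the REDCap screening form check that the shipping lag plus five weeks falls within whichever window is kept.
3. Record time since birth, or gestation, at the first session. The control panel already logs session times, so only the birth date or due date has to be linked. Adherence and pre-post change can then also be reported among women who had the full programme open to them.

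The editing, the form check and the extra field cost little. The real cost depends on the choice of window: the postpartum recruitment pool may shrink materially, since half of the present window lies beyond six months, or the programme-access wording must be extended instead.

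### Women may enrol up to 12 months after birth, but the postpartum programme is described as available up to six months, and nothing says what women at 6 to 12 months would receive

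*Protocol article*

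**What the plan says.** **Eligibility.** Participants section: "they must be pregnant (less than 36 weeks) or postpartum (up to 12 months after birth". The exclusion criteria give the same limit ("being neither pregnant (>36 weeks) nor postpartum (up to 12 months"), so 12 months does not look like a slip. The target is stated as "We aim to enroll 50 participants (25 expectant and 25 postpartum". No cap or quota by time since birth is given within the postpartum group.

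**Programme.** The NurtureVR section, under Data collection, gives the postpartum part as "five weeks postpartum (available for anyone up to six months after childbirth". In Table 1 (Study settings) the block of postpartum modules is headed "Postpartum (anyone 6 months after giving birth". That heading also refers to six months, but without the words that would make it an upper limit.

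**Delivery.** Timeline section: "VR headsets will be shipped to participants one week after the baseline questionnaire is completed", followed by "Participants will use the NurtureVR for five weeks". Neither sentence treats women at 6 to 12 months differently.

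**Analysis.** The Statistical analysis plan section specifies a general linear model for stress over time in pregnant and postpartum women. The Discussion justifies the sample size with a one-sample t-test (effect size 0.5, power 95%, alpha 0.05, 45 required, 50 planned). It also calls feasibility, acceptability and initial engagement the primary aim.

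**The concern.** A woman eight months after birth meets every stated entry criterion on timing, yet falls outside the period in which the postpartum course is described as available. The rest of Table 1 is prenatal or labour content. A reader therefore cannot tell whether she would receive the postpartum modules anyway, other content, or nothing.

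Three things depend on the answer. First, if some enrolled women are not exposed, the pre-post change in stress is diluted, and the section on analysis says these data will supply effect sizes for larger studies. Second, low use by such women would be read as poor engagement or acceptability when it came from the entry rule. Third, it is unclear which postpartum population the result describes.

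**Working it through.** **1. The plan's own figure.** For a one-sample t-test, one-sided power is P(T > t(1−α, n−1)), where T is noncentral t with n−1 degrees of freedom and noncentrality d√n. With d = 0.5 and α = 0.05:

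- One-sided: the smallest n reaching 95% is 45 (df 44, power 0.951). This reproduces the stated 45.
- Two-sided: the smallest n is 54. This does not reproduce it.
- At n = 50, power is 0.967 one-sided and 0.934 two-sided.

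The article does not state sidedness, so both are carried below. One-sided is the basis that matches the plan.

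**2. Share of the eligibility window outside stated availability.** (12 − 6)/12 = 0.50. This is a share of calendar months, not of women.

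**3. Number of women.** The article gives no distribution of time since birth at enrolment, so the possible range is 0 to 25 of 25. If entry were uniform over 0 to 12 months, 25 × 0.50 = 12.5. The one-week shipping lag is 0.23 months (4.35 weeks per month). Counting women past six months when the headset ships gives 1 − 5.77/12 = 0.519, or 13.0 of 25.

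**4. Conditional effect on power.** Suppose k women have no access and zero change, and all 50 are analysed as one group. The average effect is 0.5 × (1 − k/50).

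| Assumed share of the 25 | k | Average effect | Power, one-sided | Power, two-sided |
|---|---|---|---|---|
| 0% | 0 | 0.500 | 0.967 | 0.934 |
| 10% | 2.5 | 0.475 | 0.952 | 0.909 |
| 25% | 6.25 | 0.438 | 0.920 | 0.858 |
| 50% (uniform) | 12.5 | 0.375 | 0.834 | 0.739 |
| 75% | 18.75 | 0.3125 | 0.703 | 0.582 |

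If the women in the uniform case were instead left out of the analysis (n = 37, effect 0.5), power would be 0.910 one-sided and 0.841 two-sided.

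**The case against.** The strongest reply is that the article never says access stops at six months. Headsets go to participants without exception, and the six-month phrase sits in brackets in a product description, where it may name the intended audience. Several postpartum topics, such as emotions and stress management, are not tied to the early months. This stands. A reader might infer that women past six months have no programme to use, but the text supports only that no postpartum content is stated as available to them.

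Other tempting readings also go too far:

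- *About half the postpartum group is affected.* Half is the share of the window. It becomes a share of women only under an assumed uniform entry.
- *Women must complete baseline by about 4.6 months.* That is 6 months less six weeks (6 − 6/4.35 = 4.62) and supposes the course must be finished by six months. The wording can equally describe who may start.
- *Table 1 and the abstract confirm the limit.* The Table 1 heading could mean until or from six months. The abstract's "daily use of NurtureVR for 15 minutes during the third trimester and six weeks postpartum" concerns when or how long the programme is used, not how long it is available.
- *Power falls below 80%.* In the uniform case that holds two-sided only. On the one-sided basis that reproduces 45, power stays at 0.83. Both figures assume no access and zero change in these women, and a pooled test that the analysis section does not specify.

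It is also fair that exposure would not be hidden. The VR modules section already plans an Administrative Control Panel (ACP) log of module starts, activity times and completion. This makes the problem detectable, but it does not settle whom the entry rule should admit or how such women will be reported.

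**Conclusion.** The contradiction between 12-month eligibility and six-month stated availability is real, and nothing in the article resolves it. Followed as written, the plan can enrol women outside the described programme window, over six of the 12 eligible months. The number is unknown, from 0 to 25 of 25, and 12 to 13 under uniform entry.

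The dilution to 0.375, with power falling from 0.97 to 0.83 one-sided or from 0.93 to 0.74 two-sided, illustrates what is at stake. It requires uniform entry, no access after six months, no change in those women and a pooled analysis, and the article establishes none of these. The risk to engagement figures needs less: only that some eligible women are not offered the postpartum content. In a pilot whose Discussion puts feasibility first, that is the more direct consequence.

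**What to change.** - Confirm with the developer what access to the postpartum modules exists beyond six months after birth.
- Then reconcile the Participants section, the Table 1 heading and the NurtureVR section into one consistent postpartum window. Which window is right is for the study team, and this review does not choose one.
- For any woman enrolled past six months, record time since birth at her first session and use the planned ACP log to establish whether she was exposed.
- Report engagement and postpartum results separately for women who started at or before six months and those who started later.

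The cost is one wording amendment and one extra table. If the study team narrows the entry window, postpartum recruitment would be slightly slower.

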#### Study settings

This is a 5-week home-based study primarily using a virtual reality headset to engage in NurtureVR. Participants can set up, customize, and navigate the program through the RealizedCare mobile or web application, which serves as the platform for their participation and is free of cost to the participants. This application is compatible with any cellular device, tablet, or desktop. Mi-Fi devices will be provided to participants who do not have reliable access to Wi-Fi. Participants will be actively encouraged to use the VR headset regularly, by completing at least one module each week (see **Table 1** for module content).

**Table 1 T1:** NurtureVR module content.

Education Topic		Mindfulness Topic
Pre-natal (Before birth)		
Week 1	Power of VR on Mental Health During Pregnancy	Progressive Relaxation sequence
Week 1	Impacts of Acute and Chronic Stress During Pregnancy Techniques to Cope	Turning off Your Stress Response
Week 2	Introduction to Mindfulness and Meditation	Mindfulness: Awareness of Breath
Week 2	Staying Active During Pregnancy	Mindfulness of Body
Week 2	Sleep and Stress During Pregnancy	Relaxing & Letting Go of Thoughts
Week 3	What is a C-Section and Why Would I need it?	Being Present I (Deattachment to Outcomes*)
Week 3	Baby’s Almost Here: Enjoying the Final Weeks of Pregnancy	Mindfulness of the Life Growing Within
Week 3	Baby’s Almost Here: Advantages of Going Full Term	Being Presence II (Deattachment of Outcomes)
Week 4	Stages of Labor	The Healing Power of Breath
Week 4	Pain Management During Labor	Letting Go of Resistance to Sensations
Week 4	Should Hypnotherapy Be in the Delivery Room?	Deepening Awareness
Week 4	What is Lamaze?	Breathing Through the Whole Body
Week 5	Handling Stress and Breastfeeding	Cultivating Connection with Your Baby I
Week 5	Breastfeeding Newborn	Cultivating Connection with Your Baby II
	Lactation Support 2	Honoring Your Body As it Is
All Weeks	Baby This Week module	
Labor (Optional)	How to Use VR During Labor to Reduce Pain	
Postpartum (anyone 6 months after giving birth)		
Week 1	10 Reasons Skin to Skin is Good for Your Baby and You	Cultivating Connection with Your Baby (Redux)
Week 1	Down-There Care: Recovery from Delivery Part 1	Healing is a Powerful Piece of the Journey
Week 2	Postpartum Nutrition	Intuitive Eating/Honoring Your Body’s Needs
Week 2	Sexual Health After Pregnancy	Mindfulness as Empowerment/Acknowledging & Making Choices About Desires
Week 3	Postpartum Emotions	Riding the Waves of Emotion (Staying On Your Raft)
Week 3	How Can Mindfulness Help You and Your Baby?	Sustaining Momentum/Living in the Moment
Week 4	Don’t Let Your Newborn Ruin Your Marriage	Interpersonal Mindfulness (focus on intimacy)
Week 5	Stress Management Techniques After Delivery	Notice Tension/Resistance & Release

